## Abstract

**Background:**

Dental attendance provides an important opportunity for dental teams to explore with parents the oral health behaviours they undertake for their young children (0–5 years old). For these discussions to be effective, dental professionals need to be skilled in behaviour change conversations. The current evidence suggests that dental teams need further support, training and resources in this area. Therefore, the University of Leeds and Oral-B (Procter & Gamble Company) have worked with the local community and dental professionals to co-develop “Strong Teeth” (an oral health intervention), which is delivered in a general dental practice setting by the whole dental team. The protocol for this early phase study will explore the feasibility and acceptability of the Strong Teeth intervention to parents and the dental team, as well as explore short-term changes in oral health behaviour.

**Methods:**

Forty parents (20 of children aged 0–2 years old, and 20 of children aged 3–5 years old) who are about to attend the dentist for their child’s regular dental check-up will be recruited to the study. Parents and children will be recruited from 4 to 8 different dental practices. In the home setting, consent and baseline oral health behaviour data will be collected. The researchers will ask parents questions about their child’s oral health behaviours, including toothbrushing and diet. Three different proxy objective measures of toothbrushing will be collected and compared with self-report measures of parental supervised toothbrushing (PSB).

**Discussion:**

The parent and child will then attend their dental visit and receive the Strong Teeth intervention, delivered by the dental team. This intervention should take 5–15 min to be delivered, in addition to the routine dental check-up. Furthermore, children aged 0–2 years old will receive an Oral-B manual children’s toothbrush, and children aged 3–5 years old will receive an Oral-B electric rechargeable children’s toothbrush. At 2 weeks and 2–3 months following the Strong Teeth intervention, further self-report and objective measures will be collected in the parent/child’s home. This data will be supplemented with purposively sampled qualitative interviews with parents (approximately 3 months following the intervention) and dental team members (following delivery of the intervention).

**Trial registration:**

ISRCTN Register, (ISRCTN10709150)

**Electronic supplementary material:**

The online version of this article (10.1186/s40814-019-0483-9) contains supplementary material, which is available to authorized users.

## Background

Dental caries (tooth decay) is the most prevalent preventable childhood disease and a major public health priority [1]. Caries is a disease of health inequality. In England, 12% of 3- and 23% of 5-year-olds are affected by caries, with figures rising to 17% and 40% for children living in deprived parts of Yorkshire, respectively [2].

Both Public Health England [3] and the National Institute for Health and Care Excellence [4] identify young children and their parents as a key focus for oral health advice. Supporting parents to initiate and adopt protective home-based oral health behaviours in early-life is critical to the development of long-term oral health habits, thereby reducing common oral diseases such as caries and periodontal disease across the life course [5–7]. Both dental teams and parents [8–10] have identified that changing poor oral health behaviours for children is challenging, especially once dental disease has already been identified. Therefore, an approach which is strongly supported by local communities [11] is to encourage good oral health behaviours from the outset with different early years professionals skilled in providing appropriate support and advice. Following the development of our generic complex oral health intervention [11], our research group have adapted the intervention for different health and early years professionals. One such example is the HABIT intervention, which is focused on the universal developmental review undertaken by health visitors [12]. This home visit with parents of children aged 9–12 months covers a wide range of general health topics including a short conversation around oral health. The HABIT intervention involves training of health visitors to improve the structure, content and quality of these oral health conversations, as well as providing supporting paper-based and digital resources.

During the development of the generic and HABIT interventions, the community and study participants have repeatedly identified the need for preventive oral health conversations delivered by the primary care dental team. However, nearly two thirds (65.9%) of 0–4-year-olds did not attend the dentist in the 12 months up to June 2018 [13] and hence the need for effective oral health conversations in both the dental and community settings. These dental attendance figures are a key driver for a national oral health initiative in England, Dental Check by One (DCby1), which aims to encourage parents to take their child to the dentist before their first birthday (https://dentalcheckbyone.co.uk/) and establish regular dental attendance behaviours. The frequency of attendance is determined by the dental team based on an oral health risk assessment and can vary between 3 and 12 months [14]. Although Dental Check by One is aimed at tackling non-attendance, attendance in itself does not necessarily mean prevention advice is provided or adopted. To maximise the benefits of dental attendance, dental teams need to be able to have effective behaviour change conversations. As an example, a recent randomised controlled trial undertaken in Northern Ireland showed over a third of children developed dental caries by the age of 6 years old, despite regular attendance at the dentist over the previous 3 years [15]. In this study, preventive advice followed national Public Health England guidelines [3]. This highlights that changing oral health behaviours is challenging and requires more than simply providing information to parents.

There have been several studies that focus on the experiences of dental teams in providing oral health advice to patients [16–20]. These have identified a number of challenges, including the “ad hoc” nature of the content and delivery of oral health advice, the lack of training, knowledge and personal skills, as well as pressures related to insufficient finances, staff, facilities and time. Whilst national guidelines [3] have clarified what oral health behaviours should be promoted, they do not identify how to effectively undertake these behaviour change conversations.

Oral health behaviours (for example, brushing teeth twice a day with a fluoride toothpaste and reducing the frequency and amount of sugar consumed) are complex as they are influenced at multiple levels (i.e. individual, interpersonal, community, organisational and environmental), which can act as both barriers and facilitators to adoption [11, 21]. As such, effective oral health interventions must embrace appropriate complex intervention (traditionally defined as interventions with several interacting components) methodology, underpinned by psychological theory, as outlined by the Medical Research Council [16]. This is the approach that has been taken when developing the “Strong Teeth” intervention, such that as well as providing the evidence-based guidance provided in “Delivering Better Oral Health”, there is a strong recognition and appreciation of the challenges families with young children face and how this can impact on caring for their children’s teeth, which is based on our previous research that is underpinned by the Theoretical Domains Framework and socio-ecological model [11, 21]. For example, despite lacking the capability to effectively brush their own teeth, many young children are responsible for their own toothbrushing, yet, children are not always engaged nor co-operative with parental involvement. This is one of the reasons why in the early-phase evaluation of the Strong Teeth intervention, we have included the provision of an electric toothbrush in the 3–5 year old, as the novelty of the brush may increase child engagement with toothbrushing and parental involvement. However, accessing the acceptability and impact of electric toothbrushes in terms of engagement, toothbrushing behaviours as well as other issues, such as cost and ease of use, will be essential in the present study to determine whether this forms a key component of the intervention. The key strength of the Strong Teeth intervention is the training and focus on the conversation between dental professional and parent. Utilising a whole team approach, the conversation is tailored to the needs of each family and encourages parents to identify their own challenges and subsequently, the solutions to overcome these challenges. Yet allows each conversation to be delivered with consistency and clarity due to its structured and hierarchical format.

In collaboration with Oral-B (Procter & Gamble Company), the University of Leeds has undertaken a programme of research to develop a complex oral health intervention, delivered by dental teams to parents of young children. This programme of work included undertaking a series of rapid reviews to identify (1) the barriers and facilitators to toothbrushing, and healthy eating in respect to oral health for children aged 0–11 years old; and (2) Interventions already developed for use in general dental practice and their efficacy in reducing dental caries. As we had previously qualitatively explored the experiences of parents of children aged 0 – 6 years old [21], a second workstream explored qualitatively the experiences of dental teams (*n* = 27), parents (*n* = 37) and children (aged 7–10 years old, involving five classes in three different schools) in delivering and receiving oral health advice and what impact this had on parents’ and children’s behaviour. This was to assess what the range and scope of the intervention should be (i.e. was a combined or separate approach needed for different age groups). This work led to the Strong Teeth intervention concentrating on the 0–5 year age group. Using our earlier generic complex intervention work [11, 17, 21] in conjunction with this research, we have worked with Oral-B to co-develop the Strong Teeth intervention (https://www.dentalcare.co.uk/en-gb/strong-teeth-strong-kids). As part of a co-production approach to development, 12 focus groups with dental professionals (*n* = 4, *k* = 27) and parents (*n* = 8, *k* = 41) were undertaken to review and incrementally improve the intervention. Full details of the rapid reviews, qualitative interviews and co-production process are not in the scope of the current paper and will be reported elsewhere. Nevertheless, the Strong Teeth intervention is now finalised and ready for an early-phase evaluation to explore its acceptability to parents and dental teams, the feasibility of delivery, and whether it leads to behaviour change.

## Aims/objectives

### Feasibility study primary aim

To undertake an early-phase feasibility trial of the Strong Teeth intervention delivered by dental teams to parents of children aged 0–5 years old.

### Feasibility study primary objectives

Using a mixed-methods approach (including self-report questionnaires, dental examinations, filming the toothbrushing interaction between parent and child, and qualitative interviews):
To explore with NHS dental teams, the acceptability and feasibility of delivering the Strong Teeth intervention to parents of children aged 0–5 years oldTo review study findings against progression criteria (see Table 1) and determine whether progression to a definitive trial is appropriate

**Table 1 Tab1:** Progression criteria to definitive trial, without remedial action taken to trial design

Adoption and maintenance of appropriate oral health behaviours at 2–3 month follow-up (≥ 80%) based on self-report measures		
Intervention mechanism produces intended changes in the determinants of oral health behaviour		
Process evaluation	a	Feasibility of delivering the “Strong Teeth” intervention in a dental setting
	b	Intervention, and self-reported and objective outcome measures are acceptable to dental teams and parents
	c	Adequate recruitment (≥ 25%) of eligible families for data collection
	d	Adequate retention (≥ 85%) of consented families to data completion

### Feasibility study secondary objectives

The secondary objectives are as follows:
To explore with parents of children aged 0–5 years old the acceptability of the Strong Teeth interventionTo study the mechanisms of action for the Strong Teeth interventionTo correlate different proxy objective measures of toothbrushing with parental self-reports of parental supervised toothbrushing (PSB, i.e. the parent actively brushing their child’s teeth)To describe the changes in dietary behaviour and PSB as a result of the Strong Teeth intervention in children aged 0–5 years oldTo examine the impact of providing children aged 3–5 years old with an Oral-B electric rechargeable toothbrush, with respect to acceptability and toothbrushing behaviours

## Design/methods

This mixed-methods study will involve two participant groups: Group A—dental teams working in NHS dental practices (n = 4-8 practices) and Group B–parents of children aged 0–5 years old (*n* = 40) to allow the objectives to be achieved and to capture the perspectives of all relevant stakeholders. Involvement of participants from different backgrounds is essential to ensure the sample is representative of the local population. Therefore, this study will seek to involve parents from different socio-economic and ethnic minority groups.

### Overall design of the study

In parts of Yorkshire (Bradford, Leeds and surrounding areas) where many children are at high risk of dental caries, 40 parents who are about to attend the dentist for their child’s regular dental check-up (20 parents of children aged 0–2 years old, and 20 parents of children aged 3–5 years old) will be recruited from 4 to 8 different dental practices.

In the home setting, consent and baseline oral health behaviour data will be collected. The researcher will ask parents questions about their children’s oral health behaviours, including toothbrushing [18] and dietary behaviours [19] based on validated measures (the full baseline questionnaire can be found in Additional file 1: Appendix 1). Three different proxy objective measures of PSB will be collected and compared to self-reported parental behaviours: (1) children’s pre-brushing plaque levels per sextant [20]; (2) duration of toothbrushing and parent-child interaction during toothbrushing—the researcher will film the parent/child toothbrushing using a small action camera (GoPro HERO5, GoPro .Inc) and this will be subsequently evaluated by the research team using an established toothbrushing index, please see Additional file 1: Appendix 2 [22]; and (3) toothbrushing activity—parents will be provided with either a paper Magic Timer diary or Disney Magic Timer app for their phone/tablet, which records frequency and duration of toothbrushing. It is imperative to obtain objective as well as self-reported measures of toothbrushing as research has shown there tends to be a mis-match between reported and observed behaviours [23, 24]. The dental team member will also collect the gingivitis rating per sextant [25] and number of teeth present, missing and decayed following training and calibration using British Association for the Study of Community Dentistry (BASCD) standards [26, 27].

The parent and child will then attend their NHS dental check-up and receive the Strong Teeth intervention delivered by the dental team. The Strong Teeth resources, training manual and videos are targeted at the whole dental team to enable them to have effective oral care conversations with parents of young children in their practice. The Strong Teeth intervention serves to provide a structure and hierarchy to the conversation and can be roughly broken into three sections: (1) Check motivation—why is oral health important? (2) Check brushing technique—how to brush? (3) Identifying other barriers to oral health (e.g. healthy eating, influence of family and friends, managing the child’s behaviour to enable brushing, remembering to brush)—how to overcome these barriers? A variety of paper-based and digital resources for both dental professionals and parents are available to support the conversation (a full implementation guide, including the behaviour change techniques underlying the intervention and the Delivering Better Oral Health guidance covered by the intervention, is available from (https://www.dentalcare.co.uk/en-gb/strong-teeth-strong-kids).

Two weeks and 2–3 months following the Strong Teeth intervention, further self-reports of toothbrushing and dietary behaviours and objective measures of PSB will be collected in the parent/child’s home. This measurement schedule is shaped by the time taken for habitual behaviours to become established [28].

Recruitment and retention rates will be recorded, as this will be essential to establish the feasibility of undertaking a definitive trial (see Table 1 for the full progression criteria) The design for each group (Group A—NHS dental teams and Group B—parents of children aged 0–5 years old) will now be discussed in turn.

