### Adoption and maintenance of appropriate oral health behaviours

Changes in self-report and objective measures of PSB behaviours will be collated. The adoption and maintenance of good oral health behaviours will be measured against national guidance—for example, parental supervised toothbrushing undertaken twice a day with the appropriate amount and strength of fluoride toothpaste [3]. The validity of parent/child reports of PSB behaviours will be compared with three proxy objective measures (1–3, listed in the “Design/methods” section). We will formulate a preliminary measurement model and calculate factor loadings. Factor loadings will be available from the measurement model. By generating a standardised model where the variance of each objective measure is scaled to unity, the associate standardised factor loadings will effectively rank the measures according to the strength of their contributions to PSB. These will be taken as the quantitative assessment for each measure. The same model was used for our HABIT early-phase study and can be seen in Fig. 1 [12]. Other measures of toothbrushing behaviour (such as duration of brushing, amount and strength of fluoride toothpaste used and spitting out toothpaste residue after brushing) will be considered for inclusion in the model.

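### The timer diary or app captures only the brushings a family logs, yet the plan uses it as an objective record of brushing frequency, so logging habit cannot be told apart from brushing.

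*Protocol article*

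**What the plan says.** The section on the overall design of the study states that "Three different proxy objective measures of PSB will be collected and compared to self-reported parental behaviours". The third of these is toothbrushing activity, for which parents receive either a paper Magic Timer diary or the "Disney Magic Timer app for their phone/tablet, which records frequency and duration of toothbrushing". The same section gives the reason for having such measures, namely that what parents report and what is observed can differ: "It is imperative to obtain objective as well as self-reported measures of toothbrushing as research has shown there tends to be a mis-match".

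The article then commits the three measures to several uses:

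- **Check on self-report.** Correlating the proxies with parental self-report is a secondary objective. The section on adoption and maintenance of oral health behaviours adds: "The validity of parent/child reports of PSB behaviours will be compared with three proxy objective measures".
- **Change over time.** Measurement is repeated at home visits after baseline: "Two weeks and 2–3 months following the Strong Teeth intervention, further self-reports of toothbrushing and dietary behaviours and objective measures of PSB will be collected". The adoption section says: "Changes in self-report and objective measures of PSB behaviours will be collated".
- **Ranking.** In the measurement model, "the associate standardised factor loadings will effectively rank the measures according to the strength of their contributions to PSB".
- **Growth.** The caption of Fig. 1 describes a growth model, alongside the measurement model, for the same three measures.

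**The concern.** Neither version of the timer is described as a sensor in the brush. Both are handed to the parent. A diary entry exists only if someone writes it, and a phone or tablet timer presumably logs only when someone starts it. A brushing that was not logged leaves the same trace as a brushing that did not happen. The record is therefore the number of logged brushings, which is true brushings multiplied by the share logged.

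Two things are at stake. First, differences in the count between families, or between visits, may reflect willingness to log and not brushing. Second, independence from self-report is weak. The paper diary is a parent report, so it shares error with the questionnaire it is meant to check. The Discussion says self-report is at high risk of social desirability bias and names the size of that bias as a key evidence gap. A comparator that depends on the same parent is poorly placed to measure it.

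**Working it through.** **Plan's own figure.** The article gives no figure for timer use or logging. Its only calculated result is the interval for 85% retention with 40 parents. That reproduces as 0.85 ± 1.96 × √(0.85 × 0.15 / 40) = 0.85 ± 0.111, or 73.9% to 96.1%, and has no bearing here. All logging shares below are assumptions, so a range is shown.

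**Change over time.** Expected logged count = true brushings × share logged. The national guidance cited in the article gives 2 brushings per day as the reference. With brushing held constant at 2 per day:

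| Share logged, early → late | Logged per day | Apparent change |
|---|---|---|
| 90% → 70% | 1.8 → 1.4 | 1.4/1.8 − 1 = −22% |
| 80% → 40% | 1.6 → 0.8 | 0.8/1.6 − 1 = −50% |
| 70% → 90% | 1.4 → 1.8 | 1.8/1.4 − 1 = +29% |

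The last row shows that the error can run upwards if families log more after the dental visit.

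A real improvement can also be hidden or reversed. Suppose true brushing rises from 10 to 13 per week. If logging goes from 90% to 70%, the record shows 10 × 0.9 = 9.0, then 13 × 0.7 = 9.1. If logging goes from 80% to 50%, it shows 10 × 0.8 = 8.0, then 13 × 0.5 = 6.5.

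**Differences between families.** A simulation of one week used these assumptions:

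- Habit B is 1, 1.5 or 2 per day, with probabilities 0.3, 0.2 and 0.5.
- The true weekly count is normal with mean 7B and SD 1, limited to 0–14.
- The logged count is binomial (true count, u), with u uniform over the stated range.

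| Share logged across families | Correlation of logged count with true habit |
|---|---|
| all logged | 0.96 |
| 80–100% | 0.88 |
| 40–100% | 0.63 |
| 20–100% | 0.49 |

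A different assumed distribution of true brushing (mean about 10 per week) gives a similar pattern for the correlation of logged with true weekly count: 0.89 for 80–100% logged, 0.67 for 50–100% and 0.46 for 20–100%. In that setting the correlation of the logged count with the logging share itself is 0.24, 0.55 and 0.75. At the widest spread the count tracks logging more closely than brushing.

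**Shared keenness.** Let a trait k ~ N(0, SD) drive both logging, with logit u = 0.4 + k, and over-reporting, with self-report = B + 0.5k + N(0, 0.3) capped to 0–2 per day.

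| SD of k | Self-report with true habit | Self-report with logged count |
|---|---|---|
| 0.25 | 0.82 | 0.61 |
| 0.5 | 0.76 | 0.64 |
| 0.75 | 0.68 | 0.68 |
| 1 | 0.60 | 0.71 |

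Self-report agrees better with the timer than with the truth only when keenness varies strongly, above an SD of about 0.75. Below that, the timer makes self-report look worse than it is.

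**The case against.** The article is careful in places. It calls the measures proxies, introduces the timer under brushing activity, and says in the Discussion that the acceptability, feasibility and utility of the measures are under examination. Table 1 makes acceptability of the objective measures a progression criterion. Plaque and filmed brushing do not depend on timer use, and random failure to log would lower the timer's own loading, which the ranking is there to show. Data-handling rules may also sit in a full protocol or analysis plan that is not shown.

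Much of this stands, and the point does not rest on a missing data-handling rule. It rests on what the article states: that the tool records frequency, that it counts as objective, and that it serves the uses listed. Calling it a proxy does not separate logging from brushing. Plaque scores and a filmed session do not count daily brushings, so they cannot show whether an empty day was unbrushed or unlogged. A low loading would not reveal which of the two caused it. Error shared with self-report would not appear as a low correlation with self-report at all.

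A reader might infer three stronger claims that the document does not support:

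- **That timer use will decline over 2–3 months.** Nothing in the article says so, nor whether recording is continuous or in short blocks around visits.
- **That a day without an entry will be counted as zero brushings.** No such rule is stated.
- **That self-report will be made to look more valid than it is.** The simulation gives this only under strong shared keenness, and the opposite under mild keenness.

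**Conclusion.** The point holds as one of measurement and interpretation. The article treats a family-operated log as an objective record of brushing frequency, while the log cannot distinguish brushing from logging. This affects the comparison with self-report, the description of change and the ranking of measures. The diary version also lacks independence from the self-report it is compared with.

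The size and direction are unknown. If nearly all brushings are logged (80–100%), the loss is modest, with a correlation of 0.88. If logging varies widely (20–100%), the correlation drops to 0.49. A false fall of 22% to 50% needs logging to drop by the assumed amounts.

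The conclusion rests on two premises: that the app logs only when a family uses it, which is inferred because the article does not describe how it works, and that logging is incomplete for at least some families.

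The reach is limited. The 80% adoption criterion in Table 1 is based on self-report, and the recruitment and retention criteria do not use the timer. What is exposed is a secondary objective and the choice of measures to carry into later work.

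**What to change.** 1. Call the measure logged brushings throughout, not brushing frequency.
2. Report the logging rate (days with any entry, by diary or app) as a separate adherence and acceptability result.
3. State that a change in logged counts will not be interpreted as a change in brushing frequency.
4. At each follow-up visit, ask whether days without entries were not brushed or not timed. Use the answers only in a sensitivity analysis that sets days not timed to missing. They should not fill gaps in the main record, because they are themselves self-report and would make the comparator depend on what it is meant to check.
5. Present agreement with self-report separately for diary and app.

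Switching to duration per timed brushing would not solve the problem, since duration is also seen only for brushings the family chose to time. The question about empty days does not recover days on which only some brushings were logged, so some ambiguity remains.

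The cost is wording, one extra question at visits already planned, some missing frequency data in the sensitivity analysis, and a more cautious conclusion about the timer.
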